### Monte Carlo Simulation with patient level data approach to cost-effectiveness analysis

Initial cost-effectiveness calculations will be generated through Monte Carlo simulation to evaluate uncertainty in economic costs to caregivers and health outcomes, using an additional simulation technique to account for the uncertainty in program costs. Samples of economic costs to caregivers and health outcomes will be drawn from the data equal in size to the number of data points, with replacement. Uncertainty around program costs will be simulated by drawing data from gamma distributions derived from most likely, low and high estimates for each component. This process will be repeated 10,000 times to ensure that tails of standard error distributions are filled and increase stability in results since available computing power is sufficient. ICERs will be calculated, and uncertainty will be quantified using a bootstrap approach, choosing the values representing the upper and lower 2.5% of data. To disambiguate negative ICERs and show the probability of cost-effectiveness according to different values of the ceiling ratio, CEACs will be calculated, using per capita GNI as the reference case threshold [49] (US$1,740 in Gujarat, $571 in Uttar Pradesh). Calculations will be performed using Microsoft Excel with the Palisade at-risk add-in.

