**Conceptual framework based on Andersen and Newman [**[42]**].**

### Descriptive statistics

Descriptive statistics of the parameters (Table 3) will be calculated according to their means, confidence intervals, and *p*-values reflecting the extent of difference between arms. Comparisons will be made at the start and endpoint of the program. Stata svy commands will be used to account for clustering with *F*-tests used to evaluate the significance of differences between groups. As costs are not normally distributed, significance of differences between components listed in Table 4 at the start and end of the program will be calculated using confidence intervals with bootstrapped standard errors.

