### Health outcomes

In the standard cost-effectiveness calculation, health outcomes will be derived from incremental changes in coverage measured in cross-sectional household surveys and inputted into LiST. LiST will estimate the incremental number of lives saved from the study’s start to its completion. The years of life lost (YLL) component of disability-adjusted life years (DALYs) will be calculated using the standard formula from the Global Burden of Disease study [46]. A life expectancy estimate will be taken from WHO life tables representing the midpoint between 1–4 years old. A discount rate of 3% will be used in reference case calculations, and age weighting will not be used to be consistent with the Disease Control Priorities Project second edition (DCP2) [41]. Long-term sequelae such as acute cognitive and psychomotor development effects in young children, the effects of diarrhea on stunting [4], and obesity and related conditions that can occur later in life (cardiovascular disease and diabetes) [47] were not measured and will not be considered. The net-benefit regression approach will be limited to episodes averted as it is impossible to know the specific long-term health outcomes for individual patients. Limitations of drawing data from a single uncontrolled study are recognized [48], although cost-effectiveness analysis is often conducted on data from a single effectiveness study, and conditions in the study sites are not atypical of other relevant settings in low- and middle-income countries.

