### Net-benefit regression-based approach to cost-effectiveness analysis

A second approach to calculating cost-effectiveness will be taken according to net-benefit regression methods to control for imbalances in covariates arising from the non-randomized study design [21],[31],[32]. This method uses patient-level data of economic costs to caregivers and health outcomes, distributing program costs from the last year of the program evenly across children in the endpoint survey. A modification of the net-benefit statistic will serve as the dependent variable, given that outcomes are measured in terms of a health gap measure instead of health expectancy measure [50]. This formulation adds costs to outcomes expressed in monetary terms instead of taking the difference as is done in standard net-benefit calculations. The coefficient on a treatment variable that distinguishes between the starting point and endpoint of the program will be used to represent incremental net benefit. One sided *p*-values from the treatment variable will be used to construct CEACs, using results from a series of regressions that use different values for the ceiling ratio. Due to the non-normality in the distribution of residual values, a generalized linear model using a gamma distribution will be used. Huber-White robust standard errors will be used to address heteroskedasticity, and clustering will be accounted for consistent with study design. Data will be checked for non-linearities to assess whether use of a spline term improves model fit. The importance of influential data points will be checked using DFBETAs, excluding caregivers with the top ten DFBETA scores in sensitivity analysis. Calculations will be performed in Stata 13, using standards for good practice for using statistical regression models in economic evaluations [51].

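### The Monte Carlo approach bootstraps individual data points from clustered surveys, so the survey-derived part of its intervals is too narrow and its acceptability curves too steep if the ICC is positive

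*Protocol article*

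**What the plan says.** The Monte Carlo section of the Protocol article fixes the resampling rule for caregiver costs and health outcomes: samples of both "will be drawn from the data equal in size to the number of data points, with replacement". "This process will be repeated 10,000 times", and the interval is formed by "choosing the values representing the upper and lower 2.5% of data", which is a nominal two-sided 95% percentile interval. Program costs are simulated separately, by "drawing data from gamma distributions derived from most likely, low and high estimates for each component". The section mentions no cluster step. Its software is a spreadsheet with a simulation add-in.

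Elsewhere the same surveys are handled as clustered data. The sample-size section uses methods for cluster designs. The Descriptive statistics section uses survey commands to allow for clustering. In the net-benefit regression, "clustering will be accounted for consistent with study design". The cost comparisons in the descriptive section are "calculated using confidence intervals with bootstrapped standard errors", with no resampling unit named.

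On outcomes, the Health outcomes section says that in the standard calculation "health outcomes will be derived from incremental changes in coverage measured in cross-sectional household surveys and inputted into LiST". Lives saved from that model are then turned into years of life lost (YLL).

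**The concern.** Children in one sampling cluster tend to be alike in costs, care seeking and treatment received. Drawing single records with replacement breaks that dependence, and each draw behaves as if it came from a simple random sample of the same size. The bootstrap spread then omits the between-cluster variance. The percentile limits are too close together, and the CEAC moves too quickly from low to high probability.

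Two things are at stake. One is the stated certainty of the cost-effectiveness result. The other is the comparison of methods, which the Discussion treats as evidence of robustness. If one method allows for clustering and the other does not, their intervals and curves differ partly for that reason.

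A secondary point concerns what is resampled. The Monte Carlo section speaks of drawing health outcomes from the data, while the Health outcomes section derives them from a model fed with survey coverage. The two sections need to be reconciled.

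**Working it through.** **There is no figure of the plan's to reproduce.** The article gives no ICC, number of clusters, cluster size or power for this analysis. The only check on its own numbers is Monte Carlo error. With 10,000 iterations the standard error of a 2.5% tail is √(0.025 × 0.975 / 10,000) = 0.0016, or 0.16 percentage points. More iterations would not correct the resampling unit.

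**Formulas**, with m the analysed children per cluster:
- design effect: DEFF = 1 + (m − 1) × ICC
- interval width relative to the correct width: 1/√DEFF
- true coverage of a nominal 95% interval: 2Φ(1.96/√DEFF) − 1
- a CEAC value reported as 0.95 becomes Φ(1.645/√DEFF)

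These apply to a quantity that depends on survey data only. They assume the same DEFF in both rounds and independently drawn clusters. The article does not say whether clusters were revisited. If they were, cluster effects would partly cancel in the before-after difference and the loss would be smaller.

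**Plausible m.** Caregiver costs are collected for episodes in the last 2 weeks (Costing), and prevalence was 14% in 2011 (Strengths and limitations). If 20 to 40 children were surveyed per cluster (assumed), 0.14 × 20 = 2.8 to 0.14 × 40 = 5.6 would have an episode. If episode-free children enter with zero cost, m would be the full 20 to 40.

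**Results** (all ICC values are assumptions):

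| m | ICC | DEFF | Width ratio | True coverage | CEAC 0.95 becomes |
|---|---|---|---|---|---|
| 2.8 | 0.02 | 1 + 1.8 × 0.02 = 1.04 | 0.98 | 94.6% | 0.95 |
| 5.6 | 0.10 | 1 + 4.6 × 0.10 = 1.46 | 0.83 | 89.5% | 0.91 |
| 20 | 0.05 | 1 + 19 × 0.05 = 1.95 | 0.72 | 84.0% | 0.88 |
| 40 | 0.10 | 1 + 39 × 0.10 = 4.90 | 0.45 | 62.4% | 0.77 |

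At ICC 0 there is no loss.

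**Simulation check.** Skewed (lognormal) costs were simulated before and after, with 50 clusters of 12 per round, 400 runs and 300 resamples. At log-scale ICC 0, 0.02, 0.05 and 0.10, the individual bootstrap covered 94.5%, 92.0%, 89.8% and 82.8%. The cluster bootstrap covered 94.5%, 92.3%, 92.0% and 92.0%. The width ratios were 1.01, 0.96, 0.88 and 0.77. The ICC on the cost scale is lower than on the log scale: (e^0.10 − 1)/(e − 1) = 0.061 for the last case. That gives DEFF = 1 + 11 × 0.061 = 1.67 and a width ratio of 0.77, which agrees with the simulation. At ICC 0.02 the two bootstraps cannot be told apart. With 50 clusters of skewed costs, the cluster bootstrap also falls a little short of 95%.

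**Dilution by program costs.** Let s be the share of the naive variance of incremental cost or net benefit that comes from the surveys. The correct variance is then 1 + s(DEFF − 1) times the naive one. This equals DEFF only when s = 1, and the plan's gamma draws make s less than 1. The table is therefore an upper bound for the full result.

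**LiST effects.** If sampling has a coefficient of variation (CV) of 0.10 and the mortality effect a CV of 0.2 (both assumed), holding the effect fixed gives 0.10/√(0.10² + 0.2²) = 0.45 times the full width. This shows why the treatment of the effect should be stated. It is not an estimate for this study.

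**The case against.** The strongest reply is about size, and most of it stands. No ICC or cluster size is given, and the conceptual model is limited to children who sought care for diarrhea. The analysed clusters may therefore be small and the loss of coverage only a few points. Program-cost uncertainty dilutes the effect further. A reader might take 62% as the expected coverage. The article does not support that, because this figure needs 40 analysed children per cluster, an ICC of 0.10 and no program-cost uncertainty.

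A second reply is that a condensed article leaves resampling detail to the full plan. That does not answer the main point, because the article states the rule, at the level of data points. It has more force for the cost bootstrap in the Descriptive statistics section, where no unit is stated and the preceding sentence on tests allows for clustering. I place little weight on that passage.

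A reader might also infer that LiST outputs are resampled as if they were patient data, or that the mortality effects are held fixed. Neither is stated. The Health outcomes section suggests that coverage varies and LiST follows from it. Fixed effects would be read from silence, although the Monte Carlo section names a distribution for program costs alone. Nor does the article say that LiST will use the 23% reduction it cites, and it reports that this estimate was judged conservative against other studies.

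Finally, a reader might conclude that unequal handling of clustering ruins the comparison of methods. That goes too far. By design the methods already differ in outcome (YLL against episodes averted), covariate adjustment and handling of program costs.

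**Conclusion.** The concern holds for the resampling unit. Followed as written, the Monte Carlo section understates survey-derived uncertainty when the ICC is positive, while the regression on the same surveys allows for it. The conclusion assumes that clusters were not largely the same across rounds. The direction for the CEAC is overconfidence: probabilities are pushed away from 0.5.

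The size is unknown. Over the assumed range it runs from negligible (about 95% coverage) to serious (62%). With 3 to 6 analysed children per cluster it is about 90% to 95%, and the effect on the full interval is smaller still. The unequal handling of clustering is one avoidable difference among several between the methods, not a fatal one.

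The LiST point is secondary. The two sections should be reconciled on what is resampled, and the treatment of the mortality effects should be stated. The documents do not show that those effects are fixed.

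**What to change.** In the Monte Carlo section, replace the draw of data points with a draw of whole sampling clusters, with replacement, within state and survey round. If the same clusters were visited in both rounds, draw them jointly. In each iteration recompute caregiver costs and ORS and zinc coverage from that resample, and then derive LiST deaths and YLL. Name the sampling cluster, and report the number of clusters, the analysed children per cluster and the ICC for each state and round. Use the same unit for the bootstrapped cost comparisons in the Descriptive statistics section, or state the unit used there.

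Say that coverage is the survey quantity resampled for health outcomes. Vary the LiST mortality effects over a stated distribution or range, alongside the gamma draws for program costs.

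No new data are needed. The cost is programming and wider intervals. Running LiST in 10,000 iterations may be awkward in a spreadsheet, so the work could be more than trivial.

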Alternative methods for conducting CEA are sometimes used to evaluate a single dataset to make methodological points, assess validity, and test robustness of results according to structural uncertainty [21],[28],[29]. Two of several analytical approaches available for CEA include Monte Carlo Simulation methods with patient level data [20] and net-benefit regression [21]. The latter framework combines established methodologies from economic evaluation and econometrics and has the advantage of being able to adjust for imbalances in confounding variables. Net-benefit regression methodology can be used for randomized [21],[30] and non-randomized studies [31],[32], although the case can be made that it is even more appropriate for non-randomized study designs as covariates are more likely to be unevenly distributed across study arms [33]. Bootstrapping confidence intervals presents the problem of ambiguity in incremental cost-effectiveness ratios (ICERs), although this problem can be circumvented in both methods using the net-benefit statistic, and both net-benefit regression and bootstrapping can be used to generate cost-effectiveness acceptability curves (CEACs). The bootstrap approach offers one advantage in that uncertainty around program costs can be simulated by resampling from parametric distributions fit to the data, while program costs are divided evenly across patients within each arm in the net-benefit regression approach [21] or are assumed to cancel out across study arms or phases [31]. Deterministic calculations and net-benefit regression are commonly evaluated in tandem in the literature [21],[31],[32], but scope exists to add thought on comparisons between bootstrapping and net-benefit regression. It is anticipated that documenting thought behind choosing between these analytic frameworks will be useful to researchers facing similar questions about evaluation of programs with similar study designs.

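### The percentile interval on bootstrapped ICERs cannot be interpreted if a material share of replicates has zero or negative effect, and the net-benefit remedy the article names is not applied to it

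*Protocol article*

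**What the plan says.** The Monte Carlo section of the protocol article computes an ICER in each bootstrap replicate and sets the limits by this rule: "choosing the values representing the upper and lower 2.5% of data". On the number of replicates it says: "This process will be repeated 10,000 times to ensure that tails of standard error distributions are filled".

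A further sentence adds a safeguard: "To disambiguate negative ICERs and show the probability of cost-effectiveness according to different values of the ceiling ratio, CEACs will be calculated". The ceiling ratio is set by "using per capita GNI as the reference case threshold", US$1,740 in Gujarat and US$571 in Uttar Pradesh.

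The Background already names the difficulty, and names net benefit as the remedy: "Bootstrapping confidence intervals presents the problem of ambiguity in incremental cost-effectiveness ratios (ICERs), although this problem can be circumvented in both methods using the net-benefit".

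The denominator of the ratio is modelled. According to the Health outcomes section, "health outcomes will be derived from incremental changes in coverage measured in cross-sectional household surveys and inputted into LiST", and years of life lost are then calculated.

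**The concern.** A ratio loses the signs of its two parts. A replicate in which the programme costs more and does worse has a negative ICER, and so does one in which it costs less and does better. Sorting on the ratio places the least favourable draws next to the most favourable. Positive ratios mix in the same way: costlier and better with cheaper and worse.

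If enough replicates have a non-positive effect, the lower limit can read as cost saving when it comes from dominated draws, and the upper limit is pulled in because those draws have left the high end. The acceptability curve is a separate output and moves neither limit. The article says that net benefit avoids the ambiguity in both of its methods, yet in the Monte Carlo method the interval stays on the ratio.

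**Working it through.** The article states no ICER, interval, or mean and SE of the increments, so there is no figure to reproduce. The check has three parts.

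**1. Sign algebra.** ICER = ΔC/ΔE. Net benefit NB = λΔE − ΔC, with ΔE counted as health gained. The ΔC and ΔE values are illustrative; the λ values are the article's thresholds.

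| ΔC | ΔE | ICER | NB at 571 | NB at 1,740 |
|---|---|---|---|---|
| +100 | −1 | −100 | −671 | −1,840 |
| −100 | +1 | −100 | +671 | +1,840 |
| +100 | +1 | +100 | +471 | +1,640 |
| −100 | −1 | +100 | −471 | −1,640 |

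The ICER merges each pair and net benefit separates it. When ΔE > 0 in every replicate, ICER < λ is the same event as NB > 0, so the two agree.

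**2. Size of the distortion.** Assumption: ΔC and ΔE are independent normal, scaled to unit SE, with means zC and zE. The share of costlier-and-worse draws is Φ(−zE)Φ(zC). At zE = 1.5 and zC = 3 it is 0.0668 × 0.9987 = 6.7%, against 0.1% cheaper and better. The percentile limits below come from 4,000,000 simulated draws. The Fieller limits are the roots of (zE² − 1.96²)r² − 2·zE·zC·r + (zC² − 1.96²) = 0.

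| zE | zC | Costlier and worse | Percentile interval | Fieller interval |
|---|---|---|---|---|
| 1.5 | 3 | 6.7% | −12.7 to 17.9 | unbounded |
| 2 | 4 | 2.3% | 0.45 to 12.2 | 0.77 to 100 |
| 3 | 4 | 0.13% | 0.57 to 3.99 | 0.58 to 4.07 |
| 4 | 4 | 0.003% | 0.46 to 2.17 | 0.46 to 2.17 |

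In the first row over 99.9% of the low tail is costlier and worse. In the second row the share of bad draws lies just under the 2.5% cut, so the sign of the lower limit is unstable: in 1,000 repeats of 10,000 replicates it came out negative in about 5%. From zE = 3 upward the two methods nearly agree.

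**3. Can it happen here?** As a proxy for the share of replicates with ΔE ≤ 0, take the probability that the change in zinc coverage is not positive: P = Φ(−(p1 − p0)/SE), with SE² = D[p0(1 − p0)/(n0π) + p1(1 − p1)/(n1π)].

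- From Table 2: starting and endpoint samples of 4,200 and 5,080 (Gujarat), 3,889 and 1,001 (Uttar Pradesh).
- From Strengths and limitations: π of 14% (DAZT, 2011), or 9% (national) as a low case.
- Assumed: p0 = 1% (the sample size section says only that very few children had zinc beforehand), p1 of 5%, 10% or 20%, and design effect D of 1 to 2.

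Example, Uttar Pradesh, p1 = 5%, π = 14%, D = 1: 3,889 × 0.14 = 544 and 1,001 × 0.14 = 140 episodes. SE = √(0.0099/544 + 0.0475/140) = 0.0189, z = 0.04/0.0189 = 2.12, P = 1.7%.

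| Rise to | Gujarat | Uttar Pradesh |
|---|---|---|
| 5% | at most 0.7% | 1.7 to 11.5% |
| 10% | at most about 0.001% | 0.02 to 2.4% |
| 20% | practically 0 | under 0.1% |

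The effect also depends on ORS coverage. Assuming 30% at the start (the Background puts India below 30%), the same formula gives, for Uttar Pradesh, 13 to 26% for a 5-point rise and 1.5 to 11% for a 10-point rise. That is the ORS part alone; a large zinc rise would offset it.

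**The case against.** The strongest reply is that the authors know the problem and plan acceptability curves expressly because ratios may be negative. On such a curve a costlier-and-worse replicate counts against the programme at every positive threshold, so someone reading all the outputs together is not told that dominated draws save money. This stands: the plan does not overlook the ambiguity. It does not rescue the interval, whose limits stay as they are.

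The article also does not say how replicates are ordered across quadrants, and a fuller plan might. That is fair, but the plain reading is percentiles of the ratio, and the one remedy attached to negative ratios is the curve.

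Three stronger readings are tempting and are not supported:

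- **The interval will mislead.** This requires a material share of non-positive effects. The article has no figures that establish it, and a clear rise from near-zero zinc coverage makes it unlikely. The first scenario in the table is chosen, and cost may fall rather than rise.
- **The interval undercovers.** A simulation over seven settings (cost 0 to 3 SE, effect 1.5 to 3 SE) gave 97 to 98% coverage for the ratio percentiles and 94 to 96% for net benefit. The ratio interval is conservative there.
- **The ICER interval is the headline result.** The article calls these calculations initial and ties the thresholds to the curve.

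**Conclusion.** The point holds conditionally. As written, the interval is a percentile interval on a ratio, and it loses its meaning once replicates spread across quadrants. The distortion is negligible when the effect is about 3 to 4 SE or more above zero. It is real at about 2 SE and severe at 1.5 SE. On the article's sample sizes and the assumed coverage values, Gujarat is largely safe, and a small coverage rise in Uttar Pradesh is the likeliest trouble. The issue is interpretability, not undercoverage. These sizes rest on assumed coverage, design effect, and independent normal increments. It is a low-cost improvement to a plan that already recognises the problem: a rule fixed in advance should work whichever way the data fall.

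**What to change.** Replace the interval rule in the Monte Carlo section as follows:

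- From the same 10,000 replicates, report the 2.5th and 97.5th percentiles of incremental net benefit at US$1,740 for Gujarat and US$571 for Uttar Pradesh. State the sign convention (years of life lost averted count as positive), because the regression method uses an additive form.
- Beside the acceptability curve, report the share of replicates in each of the four cost and effect quadrants.
- Report a percentile ICER interval only if essentially all replicates have positive incremental effect. Otherwise give the ICER point estimate with the two outputs above.

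This costs a change of wording and two more summaries of replicates already drawn. It needs no new data, thresholds or simulation.
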